# MSmonitor-plus program and video calling care (MPVC) for multidisciplinary care and self-management in multiple sclerosis: study protocol of a single-center randomized, parallel-group, open label, non-inferiority trial

**DOI:** 10.1186/s12883-022-02948-z

**Published:** 2022-11-12

**Keywords:** Multiple sclerosis, MSmonitor, Quality of life, MSmonitor-plus

## Abstract

**Background:**

We designed a new multi-modal version of the MSmonitor, called the MSmonitor-Plus and Video calling Care (MPVC), a self-management and education program with e-health interventions that combines frequent use of specific questionnaires with video calling in treating multiple sclerosis (MS) patients.

**Objective:**

To assess the effectiveness, cost-effectiveness and feasibility of MPVC compared to care as usual (CAU), with the goal of achieving equal or better quality of life for MS patients and their partners/informal caregivers.

Our hypothesis is that by using MPVC, monitoring will become more efficient, that patients’ self-efficacy, quality of life, and adherence to treatment will improve, and that they will be able to live their lives more autonomously.

**Methods:**

A randomized, parallel-group, open label, non-inferiority trial will be conducted to compare MPVC with CAU in MS patients and their partners/informal caregivers. A total of 208 patients will be included with follow-up measurements for 2 years (at baseline and every 3 months). One hundred four patients will be randomized to MPVC and 104 patients to CAU. Partners/informal caregivers of both groups will be asked to participate.

The study will consist of three parts: 1) a clinical effectiveness study, 2) an economic evaluation, and 3) a process evaluation. The primary outcome relates to equal or improved disease-specific physical and mental quality of life of the MS patients. Secondary outcomes relate to self-efficacy, efficiency, cost-effectiveness, autonomy, satisfaction with the care provided, and quality of life of partners/informal caregivers.

**Discussion:**

The idea behind using MPVC is that MS patients will gain more insight into the individual course of the disease and get a better grip on their symptoms. This knowledge should increase their autonomy, give patients more control of their condition and enable them to better and proactively interact with health care professionals.

As the consulting process becomes more efficient with the use of MPVC, MS-related problems could be detected earlier, enabling earlier multidisciplinary care, treatment or modification of the treatment. This could have a positive effect on the quality of life for both the MS patient and his/her partner/informal caregiver, reducing health and social costs.

**Trial registration:**

NCT05242731 Clinical Trials.gov. Date of registration: 16 February 2022 retrospectively registered.

## Introduction

### Background

Multiple Sclerosis (MS) is a chronic inflammatory, neurodegenerative disease of the central nervous system, which leads to a range of neurological deficits. It is most commonly diagnosed in young adult patients between the ages of 20 and 40. The symptoms often include fatigue, bladder, and visual disorders, pain, impaired mobility, spasticity, sexual restrictions, and psychological disorders such as anxiety and depression [1, 2]. MS patients should therefore be treated by multidisciplinary healthcare providers (HCP’s), including e.g. MS neurologists, MS nurse specialists, rehabilitation therapists, MS urologists, and neuropsychologists [3, 4].

Clinical disease monitoring of MS treatments has three elements: disease activity as manifested in relapses (reflecting inflammation), disability (reflecting neuro axonal loss), and functionality (reflecting the degree of compensation or cerebral reserve) [5]. To detect disease activity, it is recommended that MRI follow-up be started 3–6 months after treatment has been initiated, 6–12 months after the reference scan, and then annually. At each point, a standardized semi-quantitative comparator MRI should be used [5]. The disability and functionality are determined during the consultation with the MS neurologist or MS nurse specialist and can be managed by the patient himself/herself [6].

### Rationale

HCPs around the world are faced with the need to improve patient outcomes while controlling costs. Amongst other things, there is an increasing demand for chronic disease management for an aging population. Digital transformation, a process that aims to improve an entity by triggering significant changes to its properties through combinations of information, computing, communication, and connectivity technologies” [7], is critical for healthcare organizations to improve patient outcomes and reduce costs [8]. It could lead to improvements in diagnostics, prevention, and patient therapy, ultimately enabling HCPs to use a more evidence-based approach to improve clinical decisions as opposed to care as usual (CAU), where patients consult physically with their HCPs. Real-time interactions allow a doctor to monitor a patient ‘live’, rather than every few weeks or months [8]. Operational intelligence, integration-ready applications and platforms that help manage patients, networks and employees, are easily extensible and provide a consistent and intuitive user experience, enables efficient use of healthcare resources and services, optimizing costs with the goal of improving quality of life. Information technologies that enable this goal must be extensible, secure, reliable, affordable, and tailored to the individual organization’s level of digitization [9].

The therapeutic landscape for treating MS has been made more complex with the development of newer disease-modifying therapies (DMTs). These DMTs have given HCP’s and patients a wealth of options to better manage MS during the course of the disease [10]. A study from the United Kingdom (1998–2016) [11] has shown that treatment with early intensive therapy is beneficial. It is therefore important to start the right treatment on time [11].

New DMTs are more efficacious in reducing exacerbations and may even halt progression. However, side effects and risks (e.g., thyroid disorders) must be closely monitored. More consultations in the hospital for monitoring, are not recommended for MS patients because this will increase the fatigue that many MS patients experience. This fatigue in turn leads to worsening cognitive problems (a symptom of MS) such as forgetfulness and forgetting tasks. Decrease in cognition is unfavorable for consultation with the HCP.

Self-management, a future concept in healthcare, is a process by which patients take responsibility for changing their health-related behavior / healthcare by learning about their illness and managing the physical and psychosocial consequences [12]. Digital self-management applications are part of the digital transformation in healthcare [6, 12] and could lead to improvements in diagnostics, therapy, and prevention. In the case of complex, unpredictable, and chronically progressive diseases such as MS, it is being hoped that digitization and electronic health systems (e-Health) can help more effectively diagnose and monitor individual patients to enable optimal treatment [9, 13]. Most (especially younger) MS patients have a greater digital affinity and are quite proficient at indexing and using e-health services [14–16].

Several self-management applications for monitoring symptoms and signs already exist for MS patients, as well as diaries in which patients can keep private records of their symptoms and personal notes. Kidd ea. (2017), showed that self-management interventions can improve health-related quality of life in persons with MS, with some specific evidence of improvement in depression and anxiety symptoms [17]. There is also substantial evidence now that self-management interventions lead to health benefits in long-term conditions such as diabetes, arthritis, and heart disease [18].

### MSmonitor-plus and video calling care (MPVC)

We designed a new multi-modal version of MS monitor, called MS monitor-Plus and Video calling Care (MPVC), a self-management and /education program with e-health interventions that combines more frequent use of specific questionnaires with video calling in treatment and self-management of MS patients.

In this study, we will use the digital self-management application MSmonitor, which is NEN7510 and ISO27001 certified and developed in 2009 for MS patients with a focus on online self-measurements [19–21]. MSmonitor has an educational program with e-health intervention. MSmonitor provides insight into disease symptoms, helps achieve personal goals, and aims to increase the patient’s input in shared decision-making. Thus, the patient and the HCP can work efficiently and effectively together to obtain the best possible treatment.

MSmonitor provides patients and HCP’s with qualitative disease-specific and general patient-reported outcomes. The scores are automatically calculated and displayed on a dashboard. Changes are visible at a glance [22].

We have designed a new multi-modal version of MSmonitor, MSmonitor-Plus.

The consultations consist of MSmonitor-Plus appointments. MSmonitor-Plus appointments (completion of the specific questionnaires by the MS patients with interpretation and assessment by the HCP) are scheduled every 3 months.

Each nurse specialist has his/her own MS patients for whom they perform the checks. The results from the MSmonitor-Plus are in the Electronic Patient File.

In MPVC consulting and feedback can be given to the patient via the video calling program Beterdichtbij®. Beterdichtbij is a medical video calling program that complies with the guidelines of the Doctors’ Federation KNMG and is also NEN7510:2017 and ISO 27001 certified (Beterdichtbij, Utrecht, The Netherlands) [23]. Beterdichtbij program uses Microsoft Teams, a video calling program, which is integrated into the Electronic Patient File. In this process, the patient goes from the virtual waiting room to the consulting room, where the image connection starts with the HCP [24].

The MS Monitor-Plus and Beterdichtbij are integrated into the Electronic Patient Record for easy and convenient accessibility for the HCP. It is recommended that E-health applications are connected to the Electronic Patient File to ensure that text entries are efficient and do not increase the workload (retyping of text with risk of errors) [25, 26].

Through this development – the combination of an extended version of MSmonitor with the video calling program Beterdichtbij-, a new kind of MS care has been introduced. We will evaluate the (cost) effectiveness and feasibility of this combined digital approach to MS care.

The partner/informal caregiver of the MS patient will also have the opportunity to participate in this study. For some partners/ informal caregivers living with a MS patient is quite a task. Cognitive impairment and fatigue have a significant impact on patients. Therefore, we ask the partner/caregiver to complete specific questionnaires for partners/caregivers that are related to the partner/informal caregiver’s own life, such as finances, social contacts, work, health, and level of happiness. In addition, the partner/ informal caregiver completes the Cognition Failure Questionnaire (CFQ) about his/her partner with MS (observer-reported outcome). The MS patient completes the CFQ for him/herself (patient-reported outcome).

By participation of partners/informal caregivers, we hope to obtain more relevant information about MS disease, how a person is living his/her life with MS, and coping mechanisms.

The overall objective of this study is to assess the (cost) effectiveness and feasibility of MPVC compared to care as usual (CAU), with the goal of equal or better quality of life for MS patients and their partners/informal caregivers. Our hypothesis is that by using MPVC, monitoring will become more efficient (by completing MS-specific questionnaires in advance and by using video consultations), that patients’ self-efficacy, quality of life, and adherence to treatment will improve, and that they will be able to live their lives more autonomously.

## Methods

The study will consist of three parts: 1) a clinical effectiveness study, 2) an economic evaluation, and 3) a process evaluation.

### Research questions

Each part has its own research questions.

The operationalization is presented in more detail in Table 1: Constructs and validated questionnaires.Clinical effectivenessIs MPVC, in comparison with CAU, equal or more effective in terms of quality of life (MSQOL-54), equal or more effective in terms of self-efficacy (MSSES) and other patient-reported outcomes, concerning adherence (adherence list MSmonitor), decrease in relapse frequency (Quick scan, questionnaire’ “Do I have a schub?) and severity (E-consulting, iMCQ), side effects of DMT (E-consulting, iMCQ), depression (HADS, Eq5d-5 L, iMCQ), anxiety (HADS, Eq5d-5 L), proactive coping (MSIS29, PIH, PTO) and autonomy (IPA)?Is MPVC, in comparison with CAU, equal or more effective in terms of improvement of the informal care situation, looking at burden of care (iVICQ), quality of life and happiness (CarerQol) for the informal caregiver?2.Economic evaluationWhat are the cost-effectiveness and the cost-utility of MPVC in comparison with CAU from a societal perspective? (EQ-5D-5L, iPCQ)From a hospital perspective, is MPVC, in comparison with CAU, more effective in terms of quality of care (PTO, iMCQ) and lower consultation frequency with the HCPs?3.Process evaluationHas MPVC been delivered in accordance with the protocol? And if not, what are the reasons for protocol deviation?What are the experiences and opinions of patients, informal caregivers and HCPs regarding MPVC?To what extent has MPVC impacted patients (i.e. do patients understand why it is relevant to work with MSmonitor-Plus), and has the MPVC impacted shared decision-making through consensual agreement between patient and doctor regarding the medical regimen?

**Table 1 Tab1:** Constructs and validated questionnaires

**Construct**	**Operationalization**		
	**PROM by MS monitor Plus for patients**	**PROM abbreviation**	**Ref.**
MS-Bladder disorders	Screening bladder disorders (past 7 days)	Actionable	[27]
Quality of life of patients with urinary disorders in neurologic conditions	Short Form- Qualiveen	SF-Qualiveen	[28]
For individual tension strength	Checklist	Checklist	[29]
Functioning problems of MS and the perception of these problems. Proactive coping	Multiple Sclerosis Impact Profile	MSIP	[30]
Impact of MS. Proactive coping	Multiple Sclerosis Impact Scale (past 2 weeks)	MSIS-29	[31]
Bowel problems resulting from neurogenic disorders	Neurogenic Bowel Dysfunction Score	NBD	[32]
Decrease in relapse frequency. Proactive coping	The combination MFIS-5^a^, LMSQoL^a^, and Medication and Adherence Inventory. The combined use of MFIS-5, LMSQoL, and Medication and Adherence Inventory (“Quickscan”) enables quick, monthly assessments of health-related quality of life (HRQoL), fatigue experienced, medication, and DMD adherence	Quickscan	[19]
Anxiety and depression	Hospital anxiety and depression scale	HADS	[33]
Questionnaire on intimacy and sexuality in multiple sclerosis (MS) or spinal cord injury	The Multiple Sclerosis Intimacy and Sexuality Questionnaire	MSISQ-15	[34]
MS-specific quality of life	Multiple Sclerosis Quality of Life	MSQoL-54	[35]
Check PML and check schub	Natalizumab (Tysabri) checklist		[36]
Check schub	Questionnaire “Do I have a schub?”		[29, 37]
The patient can keep track of activities and moments of rest in order to gain insight into fatigue	Diary		[37]
**Construct**	**PROMs by RMp (eCRF), for patients**	**PROM abbreviation**	**Ref.**
Questionnaire for measuring subjective cognitive functioning. The items are globally related to memory and attention	The Cognitive Failure Questionnaire	CFQ	[38]
Patient’s perception of overall health	Euroqol Vertical Visual Analogue Scale	EQ VAS, versie 2.0	[39]
Health status: Mobility, Self-care, usual activities, pain/discomfort, anxiety and depression Economic appraisal of health	Euroqol-5 Dimensions with 5 Levels	Eq-5d-5L Versie 2.0	[40]
Severity of MS Health status Proactive coping	iMTA Medical Consumption Questionnaire	iMCQ	[41]
Effect of work on illness	iMTA Productivity Cost Questionnaire	iPCQ	[41]
MS-Participation and autonomy	Impact on participation and autonomy	IPA	[42]
Self-efficacy The MSSES-Function subscale measures confidence with functional abilities, whereas the MSSES-Control subscale measures confidence with managing symptoms and coping with the demands of illness	MS Self-Efficacy Scale	MSSES	[43]
Self-management of health Information on the disease, dealing with the consequences of chronic disease, active role in consultation, and the extent to which complaints and symptoms can be monitored at home	Partners in Health Scale (Working together on health)	PIH-NL	[44, 45]
**Construct**	**Prems by RMP (eCRF) for patients**	**PREM abbreviation**	**Ref.**
Satisfaction	Patient satisfaction questionnaire Isala	PTO	[46]
**Construct**	**Proms by consultation**	**PROM abbreviation**	**Ref.**
Severity of MS, Side effect DMT	E-consulting with neurologist/nurse specialist MS		

*PROM* Patient-reported outcome measure, *PREM* Patient-Reported Experience Measure, *Ref*. reference

^a^If applicable

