**Fig. 1 Fig1:**
[figure not shown]
Flow chart of the study

**Table 2 Tab2:** Schedule of assessments concerning patients and caregivers in the intervention arm

PROMs			Standard time points									Variable time points
			B	3 m	6 m	9 m	12 m	15 m	18 m	21 m	24 m	
**ID**	**PROMs by MSmonitor Plus, for MS patients, with or without a caregiver/partner**											
1a 1b	Actionable SF-Qualiveen	Screening questionnaire for bladder disorders.	X	X	X	X	X	X	X	X	X	
		In order to assess health-related quality of life of patients with urinary disorders in neurologic conditions	X	X	X	X	X	X	X	X	X	
2	Checklist	For individual tension strength	X	X	X	X	X	X	X	X	X	
3	MSIP	Multiple sclerosis impact profile	X	X	X	X	X	X	X	X	X	
4	MSIS-29	Multiple sclerosis impact scale 29	X	X	X	X	X	X	X	X	X	
5	NBD	Neurogenic bowel dysfunction score	X	X	X	X	X	X	X	X	X	
6	Quick Scan	Five questions about the impact of fatigue on daily life, the Modified Fatigue Impact Scale-5 item Version (MFIS-5) and eight questions about health-related quality of life, the Leeds MS Quality of Life (LMSQol) and the registration of medication use	X	X	X	X	X	X	X	X	X	Every day if needed
7	HADS	Hospital anxiety and depression scale. Consists of a depression scale and anxiety scale, both are determined by means of seven questions	X		X		X		X		X	
8	MSISQ-15	Questionnaire on intimacy and sexuality in multiple sclerosis (MS) or spinal cord injury	X		X		X		X		X	
9	MSQOL-54	MS-specific quality of life	X		X		X		X		X	
10	Natalizumab checklist	16 questions every 28 days, submitted 2 days prior to the infusion of natalizumab	X									Every 28 days, if needed
11	Do I have a schub	Consists of 4 questions that the patient must answer. This shows whether he/she should contact the doctor to check if they have a schub	X									Daily available
12	Diary	The patient can keep track of activities and moments of rest in order to gain insight into fatigue	X									Daily available
ID	**PROMs by eCRF, for patients, with or without a caregiver/partner**											
13	iMCQ	iMTA Medical Consumption Questionnaire	X	X	X	X	X	X	X	X	X	
14	iPCQ	iMTA Productivity Cost Questionnaire	X	X	X	X	X	X	X	X	X	
15	CFQ	Cognitive failure questionnaire	X		X		X		X		X	
16	EQ-5D-5L	Health questionnaire (Dutch version)	X		X		X		X		X	
17	IPA	Impact on participation and autonomy	X		X		X		X		X	
18	MSSES	MS Self Efficacy Scale	X		X		X		X		X	
19	PIH	Partners in Heath Scale	X		X		X		X		X	

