	**PROMs by eCRF for caregivers/partners of MS patients**											
21	CarerQol-7D/VAS	Quality of life of informal caregivers for use in economic evaluations	X		X		X		X		X	
15	CFQ	Cognitive failure questionnaire	X		X		X		X		X	
22	iVICQ	iMTA Valuation of Informal Care Questionnaire	X				X				X	

Data collection was performed using MS monitor and eCRF. PROMs and PREMs are ordered by 1) frequency of administration and 2) alphabet

*B* baseline, *m* month

*PROM* Patient-reported outcome measure, *PREM* Patient-Reported Experience Measure

**Table 3 Tab3:** Schedule of assessments concerning the control arm

ID	PROMs		Standard time points								
			B	3 m	6 m	9 m	12 m	15 m	18 m	21 m	24 m

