### Data collection methods

Concerning the intervention group, part of the data collection is embedded within MSmonitor-Plus. For the present study, additional research questionnaires are administered via the eCRF (Tables 2 and 3). Both groups, intervention and control group, fill in questionnaires in the eCRF, at baseline and every 3 months thereafter.

Participating partners/informal caregivers fill in specific validated questionnaires for partners/ informal caregivers in the eCRF at baseline and then every 6 months.

After randomization, a study number is automatically assigned to the participant (MS patient). The study numbers of the MS patients from the intervention group are also used in MSmonitor-Plus. These study numbers can be added manually in MSmonitor-Plus under the heading: ““Characteristics”“so that we keep the patient’s data together for final data collection.

The participants’ partner/informal caregiver will receive the same study number (filled manually) as his partner with MS, except for a letter P after the number (P=Partner) so that we can keep track of participants belonging together.

Parallel to the MS patient-reported data we collect in MSmonitor-Plus and in the eCRF, we will obtain objective data such as Expanded Disability Status Scale (EDSS) scores, MS relapse, Adverse Events (Side effects of the DMT, all unrelated to Multiple Sclerosis adverse events), hospitalizations (SAE) and all contact moments (MSmonitor-Plus consultations, number of physical appointments, video calls, telephone checks, check date of completed questionnaires). Every 3 months, the investigator will record these data for each MS patient in the eCRF and in the Electronic Patient File.

Confidentiality of all data is achieved through secure storage. The MS study team and the study monitor have access to the data. The static analysis will be based on a pseudo-analyzed dataset.

Ultimately, there are 18 different research (Table 4) patients: in the control group, with and without a partner/informal caregiver, patients in the intervention group, with and without a partner/informal caregiver and partners/caregivers of patients in the intervention group and control group with the corresponding type of MS.

**Table 4 Tab4:** Overview of the research groups, with type of MS (RRMS, PPMS, SPMS)

**Intervention group (IG)**	**IG-RRMS**	**IG-PPMS**	**IG-SPMS**
MS patients (without partner/informal caregiver)	X	X	X
MS patients (with partner/informal caregiver)	X	X	X

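### Relapse frequency is assigned to two tools that do not count relapses and are scheduled only in the MPVC arm, so as operationalized it cannot be compared with CAU

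*Protocol article*

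**What the plan says.** Under Research questions, the clinical effectiveness question is framed as a comparison with CAU. It lists "decrease in relapse frequency (Quick scan, questionnaire" *Do I have a schub?* as the way relapse frequency is measured, and it points to Table 1 for the detailed operationalization.

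In Table 1 the Quickscan row carries relapse frequency (with proactive coping) as its construct. The tool is described as a combination of MFIS-5, LMSQoL and a medication and adherence inventory that "enables quick, monthly assessments of health-related quality of life (HRQoL), fatigue experienced, medication, and DMD adherence". Table 2 describes the same content: "Five questions about the impact of fatigue on daily life, the Modified Fatigue Impact Scale-5 item Version (MFIS-5"), the LMSQoL, and a registration of medication use.

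Table 2 says of *Do I have a schub?*: "This shows whether he/she should contact the doctor to check if they have a schub". After baseline it has no fixed time point and is simply available every day.

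Table 3, titled "Schedule of assessments concerning the control arm", lists neither tool, and the section on the control group says that these patients do not use MSmonitor-Plus.

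Separately, Data collection methods lists "MS relapse, Adverse Events (Side effects of the DMT" and other items as objective data, together with EDSS and hospitalizations. The investigator records these every 3 months for each MS patient. Nothing links this record to the relapse question.

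**The concern.** A between-arm outcome needs an instrument that measures the construct and is applied in both arms. The named pair fails on both counts. An analyst who follows research question 1 and Table 1 literally would have fatigue, quality-of-life and adherence scores plus triage results for MPVC, and nothing for CAU. An analyst who turns to the investigator's record can make a comparison, but from a source that the protocol does not assign to this question. Two sources are therefore on the page, and the unsuitable one is attached to the effectiveness claim.

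A smaller issue remains once the right source is used. The trial is open label, and only MPVC patients have tools that prompt contact about a possible relapse: the daily triage questions and, for natalizumab users, a checklist that Table 1 also labels as a check for a schub. Recorded relapses could then differ between arms for reasons other than true relapse frequency.

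**Working it through.** The plan states no relapse rate, effect size or power. Its only sample-size figures (93 per arm, 104 after 10% dropout) concern MSQOL-54. They reproduce: a margin of 8, SD 17.5, one-sided alpha 0.0125 and 80% power give 93 per arm with the noncentral t (power 0.804), and 93 / 0.90 = 103.3, rounded up to 104. Nothing below changes them.

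**Step 1: do the tools measure the outcome, and in whom?**

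| Source | Relapse content described | MPVC | CAU |
|---|---|---|---|
| Quickscan (Tables 1 and 2) | None: fatigue, quality of life, medication and adherence | Yes | No (not in Table 3) |
| *Do I have a schub?* (Tables 1 and 2) | Triage: whether to contact the doctor; no count | Yes | No (not in Table 3) |
| Investigator's 3-monthly record (Data collection methods) | MS relapse | Yes | Yes |

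Only the third row supports a comparison, and it is the one that research question 1 and Table 1 do not name.

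**Step 2: could the third row still be affected by ascertainment?**

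Observed rate ratio = true rate ratio × (share of true relapses recorded in MPVC / share recorded in CAU).

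The documents give none of these shares. The values below are assumptions, chosen to include equal and lower recording in MPVC. The true rate ratio is set at 0.80 for illustration.

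| CAU share | MPVC share | Observed ratio |
|---|---|---|
| 0.90 | 0.80 | 0.80 × 0.80/0.90 = 0.71 |
| 0.80 | 0.80 | 0.80 × 1.00 = 0.80 |
| 0.80 | 0.90 | 0.80 × 0.90/0.80 = 0.90 |
| 0.80 | 1.00 | 0.80 × 1.00/0.80 = 1.00 |
| 0.70 | 0.90 | 0.80 × 0.90/0.70 = 1.03 |

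A true 20% reduction is fully masked when recording is 1/0.80 = 1.25 times as complete in MPVC, diluted below that ratio, reversed above it, and exaggerated if recording is less complete in MPVC. This shows what differential recording could do, not what it will do here.

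**The case against.** The strongest reply is that the investigator's record already exists for every patient at the same 3-monthly interval, and that relapse definitions, confirmation rules and sensitivity analyses usually sit in the full protocol or analysis plan. The part about missing detail stands: the absence of a definition from a journal article is not a finding. But research question 1 and Table 1 do not merely leave the measure open. They name one that cannot serve, and the existence of a better record elsewhere does not correct that.

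A reader might infer three stronger things that the documents do not support.

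- **That MPVC raises relapse detection by design, so the comparison is biased against it.** The Abstract's discussion says only that "MS-related problems could be detected earlier", which is conditional and concerns problems in general. Earlier is not the same as more over two years. CAU patients have four hospital check-ups a year and free access to usual care. Video calls may replace physical visits in MPVC, and a triage tool can reassure as well as prompt. Neither direction nor size can be established.
- **That positive triage results will be counted as relapses.** No passage plans this; Table 1 labels that tool as a check, and Table 2 leaves the check to the doctor.
- **That a higher recorded count in MPVC can be declared in advance not to indicate harm.** With the direction of any ascertainment difference unknown, this would dismiss a possible adverse signal beforehand.

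**Conclusion.** The point holds as a mismatch between outcome and instrument. As described, the Quickscan has no relapse item, the triage tool does not count relapses, and both are scheduled only in MPVC. The stated operationalization therefore gives no between-arm comparison of relapse frequency. This rests on the documents' own tables and needs no assumption beyond reading the Quickscan as Tables 1 and 2 describe it.

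Differential ascertainment in the investigator's record is a possibility to guard against, not a demonstrated bias; the ratios shown rest wholly on assumed recording shares. Relapse frequency is one of many secondary outcomes. The sample size, the primary outcome and the non-inferiority decision all concern MSQOL-54 and are unaffected. The correction is worth making because relapse frequency is a stated effectiveness question and a suitable source is already being collected.

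**What to change.** - In research question 1 and Table 1, remove the Quickscan and *Do I have a schub?* as measures of relapse frequency, and keep both as components of the intervention.
- Name the investigator-recorded MS relapse from the 3-monthly record in Data collection methods as the source, with the same definition and the same confirmation in both arms.
- Pre-specify a sensitivity analysis limited to relapses accompanied by a documented EDSS change or a hospitalization, both already recorded. Such events should depend less on prompting. Confirmation alone can remove false positives but cannot recover relapses that were never reported.
- Interpret any difference in recorded relapses, in either direction, with possible unequal ascertainment in mind.

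The cost is a change of wording and a re-read of relapse entries in the eCRF and patient file. No new patients, visits or questionnaires are needed. The restricted analysis will have fewer events and a wider interval.
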